#### 5.3 Sample size

The sample size was calculated by PASS software (NCSS, Kaysville, UT) with sample allocation ratio of 1:1 between 2 groups with reference to other studies ( $n=94$ ). The difference in G-W score effective rate between the intervention group (96%) and the control group (77%) was 19% at 3 months, with a 2-sided 5% of type I error probability, and an 80% of power, allowing drop-out rate of 10%, a total of 110 cases were finally required for enrollment.

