## **6.4 Methodology of research subject assignment**

Patients were randomly assigned to the topologically optimized splint group or the cast group in 1:1 ratio. Random sequence list generated by SAS (Strategic Application Software, version 9.4; SAS Institute Inc) were sealed in opaque envelopes and distributed to each center. The envelope was opened in front of the patient in chronological order of the patient's visit.

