# **7 Research interventions**

## **7.1 Intervention content**

### **7.1.1 Study intervention description**

In accordance with routine clinical practice, the fracture was reduced by closed manipulation under local anesthesia. Imaging X-ray films were used to determine whether a satisfactory closed reduction was achieved after reduction. Splint and cast were used for external immobilization according to the group. Active finger activity was encouraged after immobilization. External immobilization was removed for an average of 6 weeks, and wrist rehabilitation activities commenced.

[figure not shown]

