### **7.1.3 The items and number of clinical and laboratory tests to be performed**

The fractured wrist was X-rayed examinations four times after reduction, 2weeks, 6 weeks, and 12weeks, to assess displacement and healing

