### 7.6 Research Flow Chart

|                                                 | Screening Period | Treating Period |      |       |       | Follow-up Period |
|-------------------------------------------------|------------------|-----------------|------|-------|-------|------------------|
| Time                                            | Day0             | Day3            | Day7 | Week2 | Week6 | Week12           |
| Basic information                        |                  |                 |      |       |       |                  |
| Informed Consent Form                           | √                |                 |      |       |       |                  |
| Medical history, past medical history           | √                |                 |      |       |       |                  |
| Inclusion/exclusion criteria                    | √                |                 |      |       |       |                  |
| Subjects were randomized                        | √                |                 |      |       |       |                  |
| General evaluation and safety evaluation |                  |                 |      |       |       |                  |
| visual analogue scale (VAS) scores              | √                | √               | √    | √     | √     | √                |
| Grading of swelling degree                      | √                | √               | √    | √     | √     | √                |
| radiographic parameters                         | √                |                 |      | √     | √     | √                |
| Gartland-Werley (G-W) wrist scores              |                  |                 |      |       | √     | √                |
| Adverse Event Reporting                         |                  | √               | √    | √     | √     | √                |
| Summary of research completion                  |                  |                 |      |       |       | √                |
| Drug combination                                |                  | √               | √    | √     | √     | √                |
| Other work                               |                  |                 |      |       |       |                  |
| Assign random numbers                           | √                |                 |      |       |       |                  |

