### **10.2 Analysis of primary and secondary study endpoints**

Analysis of primary study endpoints:

Gartland-Werley (G-W) score: The comparison between the two groups used Student's t-test or the Mann-Whitney U-test for continuous variables, and chi-square test or Fisher's exact test for categorical variables.

Analysis of secondary study endpoints:

Radiographic parameters: mixed linear model to test for differences between groups (participants as random effects, time and group as fixed effects).

visual analogue scale (VAS) score, swelling degree grade: mixed linear model to test for differences between groups (participants as random effects, time and group as fixed effects).

Complication: chi-square test or Fisher's exact test for categorical variables, analyzed by calculating the risk ratios and 95% confidence interval.

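### The mixed models for radiographic parameters and VAS have no Day 0 term, so the group effect is either diluted or estimated less precisely than the collected data allow

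*Protocol*

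**What the plan says.** Section 10.2 of the Protocol gives the radiographic analysis as "Radiographic parameters: mixed linear model to test for differences between groups (participants as random effects, time and group as fixed effects". The next entry gives VAS and swelling grade the same terms. Section 10.1 states them again as the general rule for repeated measurements and adds a Bonferroni correction for multiple comparisons, without saying which comparisons. Baseline values appear otherwise only in the comparability check (10.1) and the descriptive statistics (10.3).

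On timing, section 7.1.3 says "The fractured wrist was X-rayed examinations four times after reduction, 2weeks, 6 weeks, and 12weeks", so the post-reduction film is counted as one of four. In section 7.1.1, "Imaging X-ray films were used to determine whether a satisfactory closed reduction was achieved after reduction" stands after the reduction and before the splint or cast. Exclusion criterion 3 in section 6.2 judges eligibility on post-reduction radiographic values. In the flow chart (7.6), radiographic parameters are ticked at Day 0 and Weeks 2, 6 and 12. The row "visual analogue scale (VAS) scores" is ticked at Day 0 and at all five later visits.

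**The concern.** The post-reduction film precedes the device, so it cannot carry a device effect. A model with a single group coefficient and no interaction has two natural ways to handle such a value, and neither is good. If Day 0 is one of the responses, the coefficient averages a visit with no expected difference together with the visits of interest. If Day 0 is left out and not used as a covariate, a measurement already taken on every patient, and possibly a strong predictor, is discarded.

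Radiographic parameters and pain are both named in the secondary purpose (section 4). The stated model leaves open which handling applies, and the choice could be made after the data are seen.

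**Working it through.** **Inputs from the protocol.** Section 5.3: "intervention group (96%) and the control group (77%) was 19% at 3 months", two-sided 5%, 80% power, 10% drop-out, and "a total of 110 cases were finally required for enrollment". Section 6.4: 1:1 allocation. Visits: 4 radiographic and 6 VAS, Day 0 included.

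**The plan's own figure.** The pooled two-proportion formula for 96% versus 77% gives 50 per arm, 100 in total. Then 100 × 1.10 = 110, which matches (100 / 0.90 rounds up to 112 with equal arms). This sizes the primary G-W effective rate. No power is stated for the secondary models. I take 50 evaluable patients per arm.

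**Assumed, not in the documents.** Equal variance at every visit and a common correlation ρ between visits, shown over a range.

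**Dilution if Day 0 is a response.** Let k be the number of visits after Day 0. With complete data and a random intercept, the group coefficient is the difference between arms averaged over k + 1 visits. For a constant later effect δ it is (0 + kδ)/(k + 1).
- Radiographs, k = 3: 3/4 of δ, a dilution of 25%.
- VAS, k = 5: 5/6 of δ, a dilution of 16.7%.

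A simulation with 100 trials per setting and a true effect of 0.50 SD gave mean estimates of 0.37 to 0.38 (radiographs) and 0.39 to 0.41 (VAS) with Day 0 as a response. With Day 0 left out they were about 0.47 to 0.50.

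**Precision.** Variance of a patient's mean, in SD² units:
- Day 0 omitted: V1 = (1 + (k − 1)ρ)/k
- Day 0 as covariate: V2 = V1 − ρ²
- Day 0 as response: V3 = (1 + kρ)/(k + 1), for an effect shrunk by k/(k + 1)

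The worth of adjustment in patients is V1/V2 against omission, and V3/[(k/(k + 1))² V2] against Day 0 as a response. Example, radiographs at ρ = 0.5: V1 = 2/3 = 0.667, V2 = 0.667 − 0.25 = 0.417, ratio 1.60. V3 = 2.5/4 = 0.625, and 0.625/(0.5625 × 0.417) = 2.67.

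| ρ | Radiographs, vs omitted | VAS, vs omitted | Radiographs, vs response | VAS, vs response |
|---|---|---|---|---|
| 0.1 | 1.03 | 1.04 | 1.48 | 1.33 |
| 0.2 | 1.09 | 1.12 | 1.67 | 1.50 |
| 0.3 | 1.20 | 1.26 | 1.90 | 1.71 |
| 0.5 | 1.60 | 1.71 | 2.67 | 2.40 |
| 0.7 | 2.58 | 2.81 | 4.44 | 4.00 |

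**The same in power**, with the effect set so that the adjusted model has 80% at 50 per arm, for ρ = 0.1, 0.2, 0.3, 0.5, 0.7:
- Radiographs, Day 0 omitted: 79, 76, 72, 60, 41%. As response: 63, 58, 53, 40, 26%.
- VAS, Day 0 omitted: 79, 75, 70, 57, 39%. As response: 68, 63, 57, 44, 29%.

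**Weaker link to Day 0.** If later visits correlate 0.5 with each other but only r with Day 0, power with Day 0 omitted is 79% at r = 0.1, 77 to 78% at 0.2, 73 to 74% at 0.3 and 57 to 60% at 0.5.

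**The case against.** The strongest reply is that nothing in 10.1 or 10.2 says Day 0 is a response. Section 7.4 lists the follow-up evaluations without Day 0, which fits leaving it out. A reader might infer that the planned estimate is biased towards no difference; the documents do not support that without the condition. With Day 0 left out, the randomised comparison is unbiased, and chance imbalance at Day 0 is part of its variance. The Bonferroni sentence may also mean comparisons at each visit, in which case the dilution disappears, although no interaction is listed. All of this stands.

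A reader might also infer that much power is lost whichever way Day 0 is handled. That is too strong when Day 0 is omitted: at correlations of 0.1 to 0.2 the loss is 1 to 5 points from 80%. Low correlations are plausible, because exclusion criterion 3 truncates the post-reduction values and Day 0 pain is acute-injury pain set against pain up to Week 12.

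Nor do the documents support the reading that a real loss of alignment would pass as equivalence: the protocol states no equivalence claim or margin. For VAS, the flow chart puts the score, randomisation and device distribution on Day 0 without an order, so it is not established that Day 0 VAS precedes the device.

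A further reply is that baseline terms belong in the SAP, which is not at hand. That carries less weight, since the protocol itself fixes the model terms, twice, and the terms it fixes can be improved at almost no cost.

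**Conclusion.** The point holds in conditional form. The listed terms omit a baseline value scheduled for every patient. The 1/4 and 1/6 dilutions are exact for a constant later effect with complete data, a main-effects model and Day 0 as a response. If the effect varies, for instance after the device comes off at about 6 weeks, the same fractions apply to the average later effect and not to any one visit. For VAS they also need a Day 0 score taken before the device.

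If Day 0 is omitted, the cost is precision only: negligible to modest at correlations up to 0.2, and substantial from about 0.3 to 0.4 upwards. The correlation is an assumption throughout. Only secondary endpoints are touched: the G-W score has no Day 0 value, and the sample size of 110 is unaffected.

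**What to change.** In sections 10.1 and 10.2, state that Day 0 is not a response with a free group effect. Either fit the post-baseline visits with the patient's own Day 0 value as covariate (the post-reduction film for each radiographic parameter, the Day 0 score for VAS), or keep Day 0 in the model with the two arms constrained to a common Day 0 mean. Add a group-by-time term and name the visit at which the groups are compared; without it, the covariate version still averages over all follow-up visits. Say which comparisons the Bonferroni correction covers. For VAS, confirm in section 7.6 that the Day 0 score is taken before the device is applied.

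The cost is a baseline term, the interaction and a few sentences of text, with no new data or visits.

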## **10 Statistical Analysis**

### **10.1 General Method**

During statistical analysis, the following steps will be taken: first, an examination of the number of completed cases and dropout status of the patients; then, an analysis of the baseline characteristics related to demographics for the two groups at the time of patient inclusion, assessing comparability between the study group and the control group; efficacy evaluation will involve determining efficacy indicators and comparing the efficacy between the two groups; safety evaluation will include a comparison of laboratory indicators and clinical adverse reactions.

All statistical tests will be two-tailed, and a p-value less than or equal to 0.05 will be considered statistically significant for the tested differences.

Data analysis was consistent with the principle intention-to-treat (ITT) of per-protocol (PP). For quantitative variables, descriptive statistics will include means, standard deviations, medians, minimum values, maximum values, lower quartiles (Q1), upper quartiles (Q3), and for categorical variables, the description will include counts and percentages for each category.

Comparisons between the two groups for general characteristics will be analyzed using appropriate methods based on the type of indicator. The comparison between the two groups used Student's t-test or the Mann-Whitney U-test for continuous variables, and chi-square test or Fisher's exact test for categorical variables. For repeatedly measured data, we used a linear mixture model for statistical analysis, with participants as random effects, time and group as fixed effects, multiple comparisons of data were correction by Bonferroni. Complications were analyzed by calculating the risk ratios and 95% confidence interval.

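### The ordinal swelling grade is given a Gaussian linear mixed model with main effects only; visit-level standard errors can be wrong in either direction, and a Day 0-inclusive group effect is diluted

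*Protocol*

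**What the plan says.** Section 10.2 puts the swelling grade on the same line as pain: "visual analogue scale (VAS) score, swelling degree grade: mixed linear model to test for differences between groups". Section 10.1 gives the terms for all repeatedly measured data: "with participants as random effects, time and group as fixed effects, multiple comparisons of data were correction by Bonferroni". Neither section names a group-by-time term, a baseline covariate, an ordinal model or a residual covariance structure.

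Section 7.6 lists the outcome as "Grading of swelling degree" and schedules it at Day 0, Day 3, Day 7, Week 2, Week 6 and Week 12. No section defines the grades, their number or their expected distribution. Section 4 names swelling in the secondary purpose.

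Elsewhere Section 10.1 chooses methods by type of variable, with "chi-square test or Fisher's exact test for categorical variables".

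**The concern.** A grade is an ordered category. A linear mixed model treats the steps between grades as equal and, in its ordinary random-intercept form, gives every visit the same variance. Swelling after a fracture would be expected to settle over 12 weeks, so grades should move towards the lowest level and their spread should change between visits. One pooled variance would then be too large at some visits and too small at others.

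The written model also produces one group effect for the whole period. Swelling is measured before treatment could act, at Day 0, and the model has no baseline term. If Day 0 enters as an outcome, a visit with no expected group difference is averaged into the effect.

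At stake is how a named secondary result can be read: a false signal at one visit, an uninformative interval at another, or a real difference averaged down.

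**Working it through.** **The plan's own figure.** The protocol states no figure for swelling. Its one planned number, 110, is for the primary endpoint ("The difference in G-W score effective rate between the intervention group (96%) and the control group (77%) was 19% at 3 months"). The pooled two-proportion formula gives n per arm = [1.96·√(2·0.865·0.135) + 0.842·√(0.96·0.04 + 0.77·0.23)]² / 0.19² = 49.6, so 50 per arm and 100 in total. Then 100 × 1.10 = 110, or 100/0.9 = 112 rounded up to whole patients. The figure reproduces and is used here only to set about 50 evaluable per arm.

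**Inputs.** From the protocol: six visits, 1:1 allocation, two-sided 5%, Gaussian mixed model with a participant random effect, Bonferroni. Assumed, because the protocol is silent: four grades (0 to 3), the distributions below, no treatment effect, complete data, one common residual variance, and group-by-visit means so that visit contrasts exist.

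Percent at grades 0/1/2/3:

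| Scenario | Day 0 | Day 3 | Day 7 | Week 2 | Week 6 | Week 12 |
|---|---|---|---|---|---|---|
| A, spread early | 5/20/40/35 | 5/25/40/30 | 10/35/35/20 | 30/40/25/5 | 75/20/5/0 | 95/5/0/0 |
| B, most in top grade early | 0/2/13/85 | 0/3/17/80 | 3/22/50/25 | 20/45/30/5 | 65/28/7/0 | 90/10/0/0 |
| C, most in one middle grade early | 0/10/80/10 | 0/10/80/10 | 5/30/55/10 | 25/40/30/5 | 50/30/15/5 | 80/15/5/0 |
| D, strong early ceiling | 0/0/5/95 | 0/0/10/90 | 0/10/40/50 | 15/35/35/15 | 50/30/15/5 | 80/15/5/0 |

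**Formula.** Let v_t be the grade variance at visit t and v̄ its mean over the six visits. With complete data, the random-intercept model assigns each visit difference the variance (2/n)·v̄, while the true variance is (2/n)·v_t. So

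- ratio of model SE to true SE = √(v̄ / v_t), in which n cancels;
- true size of a nominal 5% test = 2[1 − Φ(1.96 × ratio)].

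**Example, scenario A.** The variances are 0.7475, 0.7475, 0.8275, 0.7475, 0.3100 and 0.0475, so v̄ = 3.4275/6 = 0.571. Day 7: √(0.571/0.8275) = 0.83, size 10.3%. Week 12: √(0.571/0.0475) = 3.47, size 0%.

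**Results, ratio (true size):**

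| Scenario | Day 0 | Day 3 | Day 7 | Week 2 | Week 6 | Week 12 |
|---|---|---|---|---|---|---|
| A | 0.87 (8.7%) | 0.87 (8.7%) | 0.83 (10.3%) | 0.87 (8.7%) | 1.36 (0.8%) | 3.47 (0.0%) |
| B | 1.40 (0.6%) | 1.23 (1.6%) | 0.78 (12.7%) | 0.74 (15.0%) | 0.96 (5.9%) | 1.99 (0.0%) |
| C | 1.50 (0.3%) | 1.50 (0.3%) | 0.94 (6.5%) | 0.79 (12.2%) | 0.76 (13.8%) | 1.25 (1.4%) |
| D | 2.96 (0.0%) | 2.15 (0.0%) | 0.97 (5.6%) | 0.70 (17.0%) | 0.73 (15.4%) | 1.20 (1.8%) |

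A simulation of 8,000 null trials per scenario (50 per arm, latent within-participant correlation 0.5) agrees: ratios within 0.04 and sizes within about half a percentage point. With Bonferroni over six visits, the simulated familywise error was 8 to 12% against 5%.

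**The group effect as written.** With complete data this is the difference in participants' mean grade over the visits. Its standard error comes from the observed spread of those means, so unequal visit variances do not distort it. In the simulation its SE ratio was 1.00 to 1.01 and its size 4.6 to 5.4%.

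**Dilution.** Randomisation makes the expected Day 0 difference zero. If the true difference is δ at all five later visits, the six-visit average is 5δ/6 = 0.83δ. If it is δ at Days 3 and 7 only, the average is 2δ/6 = 0.33δ, against 2δ/5 = 0.40δ over post-baseline visits and δ at those two visits themselves. This assumes that Day 0 is counted as an outcome visit; the protocol does not say.

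**The case against.** The strongest reply is that the written model has no group-by-time term, so it yields one group effect and no visit-level standard errors, and the test of that effect holds its 5% level. That stands. The visit-level errors arise only if visit contrasts are made. The Bonferroni sentence suggests them, since a single two-arm effect needs no such correction, but it does not define them.

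Second, no residual covariance structure is stated, and that detail is commonly left to a SAP, which is not at hand. Visit-specific or robust variances would be compatible with the text and would cure the standard errors. This also stands: the silence is not a fault, and the constant variance is an assumption here. What the protocol does fix is the Gaussian model for a graded outcome, with main effects only.

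Third, a reader might infer that the intervals are too narrow at the early visits and too wide once swelling has resolved. The documents do not support the first half. It appears at Days 0 and 3 only in scenario A. In B, C and D the ratios there are 1.23 to 2.96, and the inflated error moves mainly to Week 2, with Day 7 or Week 6 in some scenarios. Nor does the protocol say that the splint should act on swelling mainly in the early visits.

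**Conclusion.** The point holds as a modest one on a secondary endpoint. The protocol assigns an ordinal grade to a linear mixed model with time and group main effects.

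- The averaged group test is valid in size. It would be wrong to conclude that the planned swelling test as written has inflated type I error.
- It answers a blunt question. If Day 0 is counted as an outcome, a constant later effect shrinks by one sixth.
- If visit comparisons are made under a constant residual variance, their standard errors are unreliable in both directions. All four assumed distributions give intervals too wide at Week 12 (ratio about 1.2 to 3.5), and all give intervals too narrow where the grades are most spread (about 0.70 to 0.88, true size about 8 to 17%). Bonferroni does not repair this.

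The sizes rest on assumed grade levels and distributions. That a pooled variance misstates visits with unequal spread follows from the formula; which visits those are cannot be read from the protocol. The primary Gartland-Werley analysis is not touched.

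**What to change.** In Section 10.2, separate the swelling grade from the VAS line. Analyse post-baseline grades with a cumulative-logit (proportional-odds) mixed model containing a participant random effect, group, visit, group-by-visit and the Day 0 grade as covariate, and report odds ratios by visit. Define the grade levels, and set in advance how sparse grades at late visits are collapsed. State which visit comparisons the Bonferroni correction covers.

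If a linear model is preferred, keep it with visit-specific or robust variances and the same Day 0 and group-by-visit terms. That corrects the standard errors but still treats the grade steps as equal.

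The cost is a sentence or two and standard software. No new data are needed, since Day 0 swelling is already collected. The small downsides are sparse grades late in follow-up and reliance on proportional odds. The change does not touch the VAS or radiographic analyses.

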### **10.3 Baseline descriptive analysis**

Baseline information for both groups was recorded as descriptive statistics. Continuous variables are expressed as mean  $\pm$  standard deviation, categorical variables are expressed as percentages, and skewed variables are expressed as medians (IQR).

